#### Exploratory outcomes

*Time from randomization to occurrence of myopia (time-to-event outcome)*: The time from randomization to the occurrence of myopia will be measured as a time-to-event outcome. This endpoint will provide further insights into how quickly DIST delays the onset of myopia compared to the control group.*The association between near-work duration at home and myopia onset*: The duration of near-work activities (e.g., reading, using electronic devices) at home will be correlated with the onset of myopia to investigate environmental factors influencing myopia development. This data will help clarify the role of lifestyle factors in conjunction with DIST intervention.*The association between device usage duration and myopia onset*: The duration of DIST device usage will be correlated with the onset of myopia to explore potential dose–response relationships. This will determine whether longer usage of DIST is associated with a greater effect on myopia prevention, while controlling for other near work behaviors.*Changes in choroidal thickness (ChT) (µm) at 6 and 12 months follow-ups*: Changes in choroidal thickness will be monitored as an exploratory endpoint to assess the potential underlying physiological mechanisms of DIST technology in myopia prevention. Changes in choroidal thickness or blood flow as biomarkers of myopia progression are of significant importance in myopia prevention and control research.*Side effects and adverse events*: The occurrence of side effects and adverse events will be closely monitored throughout the study to ensure the safety of the DIST intervention. This will include any ocular or systemic issues reported by participants, and the severity of these events will be recorded.

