#### Adjustment for dropout and attrition

Considering an anticipated dropout rate of 20%, the final required sample size per group is the following:Adjusted sample size per group: 64 participants.Total sample size for three groups: 192 participants.

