## Statistical methods

### Statistical methods for primary and secondary outcomes {20a}

Analysis of primary outcomeIn this participant-based study, the primary outcome is the proportion of myopia onset. This outcome is measured as a binary (nominal) variable. Participants are classified as either having experienced the onset of myopia (Yes) or not (No), based on whether their cycloplegic spherical equivalent refractive error reaches or exceeds − 0.50 D in either eye at the 1-year follow-up. This is a single endpoint measure, assessed once at the end of the 1-year follow-up period. It provides a proportion of participants who experience the onset of myopia. To test the effectiveness of DIST on the primary outcomes, logistic regression including trend analysis will be used, which can both examine the overall relationship and detect potential trends related to different treatments. In addition, covariates such as baseline spherical equivalent refractive error, age, gender, and study group (Intervention vs. Control) will be included to ensure a parsimonious logistic regression model while controlling for factors known to influence myopia onset and progression.The primary analysis will be conducted on the ITT population, which is defined as all randomized participants with at least one post-baseline measurement. For all analyses, the underlying model assumptions will be rigorously evaluated. For instance, when applying logistic regression to assess the binary primary outcome, we will verify the linearity of the logit for continuous covariates using methods such as the Box–Tidwell test, assess multicollinearity via variance inflation factors (VIF), and examine residuals and influence statistics (e.g., Cook’s distance) to identify any influential outliers. Missing data will be addressed using multiple imputations by chained equations under the assumption of data missing at random (MAR), with sensitivity analyses planned to assess the impact of outliers, nonadherence, and loss to follow-up.Analysis of secondary outcomesThe secondary outcomes are intended to capture aspects of the intervention effect that are not fully reflected by the primary outcome. For example, even if the primary outcome (myopia onset) does not show a statistically significant difference, significant changes in spherical equivalent or axial length may still be observed, thereby indicating a potential benefit of the intervention in slowing myopia progression.For the three secondary outcomes: (1) the proportion of fast progressors over 1 year, (2) changes in spherical equivalent progression, and (3) changes in AL (mm) at each follow-up point, the following statistical procedures will be employed:Proportion of fast progressors (binary outcome)This endpoint will be analyzed using logistic regression. The model will estimate the odds of being classified as a fast progressor over 1 year, comparing the intervention group to the control group. Covariates to be included in the model are baseline spherical equivalent refractive error (continuous), age (continuous), and gender (categorical), as these factors have been shown in prior research to influence myopia progression. The study group (intervention vs. control) will be the primary factor of interest. These covariates are selected based on their theoretical relevance and empirical support, ensuring a parsimonious model that controls for potential confounding without overfitting.Changes in spherical equivalent progression (continuous outcome)The change in spherical equivalent progression over time will be analyzed using a repeated measures mixed-effects model. This model will account for within-subject correlations across multiple follow-up points and will include fixed effects for the treatment group, time (as a categorical or continuous variable depending on the observed pattern), and the interaction between treatment and time. Baseline spherical equivalent refractive error, age, and gender will be included as covariates to adjust for initial differences and known predictors of refractive change. The rationale for these covariates is their established association with myopia progression, ensuring that the model is both explanatory and parsimonious. Model selection procedures, such as stepwise backward elimination based on the Akaike Information Criterion (AIC) or likelihood ratio tests, will be applied to refine the final model.Changes in AL (mm)Similar to the spherical equivalent endpoint, changes in axial length (measured in mm) at each follow-up will be analyzed using a repeated measures mixed-effects model or an analysis of covariance (ANCOVA) for longitudinal data. The model will include fixed effects for treatment, time, and their interaction. Covariates will include baseline axial length, baseline spherical equivalent, age, and gender. These factors are chosen because they are known to influence ocular growth and, consequently, axial elongation. As with the other endpoints, a parsimonious model will be achieved by using stepwise selection methods or likelihood ratio tests to retain only covariates that contribute significantly to explaining the variation in axial length change.The results of these analyses will be presented as adjusted odds ratios with 95% confidence intervals for the binary outcome and as least-squares means (LSMEANS) with standard errors for the continuous outcomes. In addition, p-values will be reported to assess the statistical significance of the observed differences between intervention groups.Analysis of exploratory outcomesTime-to-myopia onset analysisFor comparing the time to myopia onset (time-to-event outcome) among 3 treatment groups, we all create a number-at-risk table and use the Kaplan–Meier method to estimate survival curves, followed by the log-rank test to assess differences statistically.Myopia onset associationsA logistic regression model will be built with myopia onset as the dependent variable and near-work duration, device usage duration, and confounding factors as independent variables. The near-work duration was derived from the near-work log cards and questionnaires, with the daily averages taken for analysis. Odds ratio (OR) and its 95% confidence interval will be estimated to determine associations while controlling for confounding.Dose–response relationship analysisWe will group near work and device usage durations (e.g., by quartiles). Use the Cochrance–Armitage trend test to analyze if there’s a dose–response relationship. Curve fitting (such as polynomial regression) can also be used to further explore the non-linear relationship between them.Choroidal thickness changesFor exploring changes in choroidal thickness during different follow-up periods among three groups, repeated measures analysis of variance (ANOVA) will be used. If significant effects are found, post hoc tests (like Bonferroni or Tukey’s) will determine specific differences.

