#### ITT analysis (primary result)

The ITT analysis will be carried out to reflect the real-world application effect of the devices in preventing myopia onset. In case a participant drops out or has missing data during the follow-up period, we will use the Last Observation Carried Forward (LOCF) method. This ensures that all randomly assigned participants are retained in the analysis, maintaining the integrity of the randomization and providing a comprehensive view of the overall effect of the devices in a real-life scenario.

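### Choroidal thickness is assigned repeated-measures ANOVA, which needs complete or imputed records, and no missing-data rule is clearly tied to it; the mixed model already specified for spherical equivalent avoids the problem

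*Protocol article*

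**What the plan says.** All three analysis methods stand in the protocol article, Statistical methods {20a}.

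- **Choroidal thickness:** "repeated measures analysis of variance (ANOVA) will be used" to compare the three groups over follow-up, with Bonferroni or Tukey tests if an effect is found. No covariates are mentioned.
- **Spherical equivalent (SE):** "The change in spherical equivalent progression over time will be analyzed using a repeated measures mixed-effects model". The model has group, time and their interaction, with baseline SE, age and gender as covariates.
- **Axial length:** "will be analyzed using a repeated measures mixed-effects model or an analysis of covariance (ANCOVA) for longitudinal data", with a similar covariate list plus baseline axial length.

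The Outcomes section gives the status of the measure: "Changes in choroidal thickness will be monitored as an exploratory endpoint", to look at the mechanism of the device. Table 1 schedules OCT at enrolment, 6 and 12 months, and not at 3 months.

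On missing data, the primary-outcome paragraph of {20a} says: "Missing data will be addressed using multiple imputations by chained equations under the assumption of data missing at random (MAR"). Section {20c}, under the ITT analysis, says instead: "we will use the Last Observation Carried Forward (LOCF) method". The per-protocol analysis excludes incomplete children. The sample size section expects 20% dropout ("Considering an anticipated dropout rate of 20"%).

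**The concern.** Classical repeated-measures ANOVA works on complete rows. A child scanned at enrolment and 6 months but not at 12 months has an incomplete row, and by default the 6-month scan is lost with it. A mixed model keeps that scan.

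What happens here depends on a rule that the article does not tie to this outcome. The multiple-imputation sentence sits in the primary-outcome paragraph, and the ITT and per-protocol text of {20c} is framed around delaying myopia onset. The two rules also disagree. If neither applies, observed scans are discarded, and the result is biased when leaving depends on earlier thinning. If LOCF applies, a 6-month or even an enrolment thickness is analysed as the 12-month value; a carried enrolment value is a change of exactly zero.

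At stake is the reading of the mechanism result beside SE and axial length. The efficacy conclusions are not at stake.

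**Working it through.** **Base figure.** The article gives no calculation for choroidal thickness, so the only sample size to reproduce is that of the primary outcome. With rates 0.54 and 0.21, margin 0.05, α = 0.0125 and 80% power (unpooled variance):

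n = [0.54×0.46 + 0.21×0.79] × (2.241 + 0.842)² / (0.33 − 0.05)² = 50.2, rounded up to 51. Then 51/0.80 = 63.75, rounded up to 64 per arm.

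This agrees with the stated figures of about 50 and 64. It serves here only as the source of 64 children per arm and 20% dropout.

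**What each missing-data route does to the ANOVA**

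| Route | Effect on choroidal thickness |
|---|---|
| No rule applied | Children lacking an OCT visit are deleted |
| Multiple imputation under MAR | Children are kept; most of the harm disappears |
| LOCF | Children are kept; an earlier thickness becomes the 12-month value |
| Per-protocol exclusion | Incomplete children are removed, as stated |

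**Children contributing when nothing is imputed.** The split of dropout is an assumption.

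- Complete records per arm: 64 × 0.80 = 51.2 (192 × 0.80 = 153.6 in total).
- If half the dropout (10%) follows the 6-month visit, children with a 6-month scan: 64 × 0.90 = 57.6.
- Difference 6.4 per arm; ratio 57.6/51.2 = 1.125.
- Range over all splits: 0 extra children (all lost before 6 months) to 12.8 (all lost after).

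**Precision at 12 months.** Let r be the 6/12-month correlation given baseline, and n6 and n12 the numbers seen at each visit. With dropout only in one direction, the likelihood-based variance of the 12-month mean, relative to complete cases, is n12 × [(1 − r²)/n12 + r²/n6].

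- r = 0.7, n6 = 57.6, n12 = 51.2: 0.51 + 0.49 × 51.2/57.6 = 0.946, about 5% less variance.
- r from 0.3 to 0.9, all splits: 0 to 16% less.

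**Bias of complete cases.** This was simulated with no true group effect, a 6/12-month correlation of 0.7, and leaving after 6 months related to thinning in one arm only. The share leaving among those seen at 6 months is 6.4/57.6 = 11%. All settings except the 20% dropout are assumptions.

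| Log-odds of leaving per SD of thinning | False difference, 6 months | False difference, 12 months |
|---|---|---|
| 0.25 | 0.03 SD | 0.02 SD |
| 0.5 | about 0.05 SD | 0.04 SD |
| 1 | 0.10 SD | 0.07 SD |

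Under the same mechanism the likelihood-based 12-month estimate was off by only about 0.001 SD. For scale, the standard error of a two-arm difference with 51.2 per arm is √(2/51.2) = 0.20 SD.

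The size of the LOCF error cannot be given, because the article states no expected thickness change.

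**The case against.** A reader might infer that this plan drops every child with a missing visit. The documents do not support that. The article names multiple imputation and LOCF, and {20c} says that LOCF keeps all randomised children in the ITT analysis; only the per-protocol analysis excludes. If either rule reaches choroidal thickness, no child with a post-baseline scan is deleted. Missing the 3-month visit costs nothing here, since no OCT is scheduled then. Deletion is the default of the method, not a stated rule of this plan.

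Three further points stand. First, saying nothing about covariates for choroidal thickness does not exclude them; a condensed article may leave them to the full protocol or analysis plan. Second, the bias scenario is deliberately unfavourable, with selection in one arm only, and even its largest value is about half the standard error of the comparison. Third, the outcome is exploratory, and the Discussion says that mechanisms need further work.

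What the objection does not remove is that the article fixes a named method that depends on complete or filled-in records, while its own rules for filling them in conflict. Multiple imputation would largely solve the problem, but it cannot be presumed when LOCF is named for the ITT analysis. No reason is given for leaving the model used for SE.

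**Conclusion.** The point holds as a low-severity weakness. Repeated-measures ANOVA is a stated choice for choroidal thickness, and its handling of a missed OCT visit is left open between deletion, LOCF and multiple imputation.

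If nothing is imputed, the cost is 0 to 12.8 children per arm at 6 months (6.4 with an even dropout split) and a 0 to 16% loss of efficiency at 12 months. Under one-sided selection the bias is about 0.03 to 0.10 SD at 6 months and 0.02 to 0.07 SD at 12 months. These figures rest on the assumed dropout split, selection strength and correlation; only the 64 per arm and the 20% come from the article. Under multiple imputation most of this cost would vanish. No primary or secondary conclusion is affected.

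**What to change.** Replace the ANOVA sentence with the model already specified for SE:

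- outcome: change in choroidal thickness at 6 and 12 months;
- fixed effects: group, visit and group-by-visit;
- covariates: baseline choroidal thickness, baseline SE, age and gender;
- data: all observed visits, with no LOCF;
- group comparisons: pairwise contrasts taken from this model, in place of separate post hoc tests.

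This settles missed scans for choroidal thickness whichever way the imputation and LOCF statements are reconciled elsewhere. The cost is one or two sentences of analysis text. The same model code is needed for SE anyway, and no visit, measurement or sample size changes.

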
### Interim analyses {21b}

N/A

### Methods for additional analyses (e.g., subgroup analyses) {20b}

Subgroup analysis will be conducted based on the total duration of near work and the usage duration of devices in this study. The aim is to explore the impacts of these two factors on AL growth and the incidence rate of myopia among the subjects.

Firstly, we will divide the subjects into different subgroups according to specific criteria regarding the durations of near work and device usage.

Then, appropriate statistical methods will be employed for the analysis. To analyze the impact on the AL growth, which is a continuous variable, we will consider using analysis of variance (ANOVA) or regression analysis to compare the differences in AL changes among different subgroups and to determine whether there are significant associations between the durations of near work/device usage and the AL growth. In this process, relevant covariates such as age, gender, baseline refractive status, and outdoor activity time will be adjusted to control for potential confounding effects.

For the analysis of the impact on the incidence rate of myopia, which is a binary variable, logistic regression will be utilized. The myopia incidence will be set as the dependent variable, while the durations of near work and device usage will be the main independent variables. Additionally, the same set of covariates as mentioned above will be included in the model to account for confounding factors and to obtain more accurate estimates of the odds ratios and their corresponding confidence intervals, which can reflect the strength and significance of the associations between these factors and the myopia incidence.

Furthermore, interaction terms between the durations of near work and device usage might be considered in the models to explore whether there are combined effects of these two factors on the outcomes of interest. Through this comprehensive subgroup analysis, we expect to gain a more detailed and in-depth understanding of how the durations of near work and device usage influence the AL growth and the myopia incidence among the subjects.

### Subgroup analysis of secondary outcomes

Subgroup analyses will be conducted to investigate two primary factors among pre-myopic children: (1) the total duration of device usage, and (2) the duration of near work. The objective is to determine how these factors affect key myopia prevention indicators—including the primary endpoint (proportion of myopia onset) and secondary outcomes (proportion of fast progressors, change in spherical equivalent progression, and change in axial length).

### Stratification and definition

Participants will be stratified into subgroups based on predetermined thresholds for both device usage and near work duration. For the purposes of this study, we will operationally define high-intensity near work behavior as a daily at-home near work duration of 2 h or more, while near work behavior lasting less than 2 h per day will be classified as low-intensity.

All participants will be included in the analysis. Adherence, defined as the ratio of actual device usage duration to planned usage duration, is calculated as both daily (daily adherence (%) = actual daily training duration/planned daily training duration × 100%) and overall (overall adherence (%) = ∑ (actual daily training duration)/∑ (planned daily training duration) × 100%). Subsequently, according to the adherence categories established by the Pediatric Eye Disease Investigator Group (PEDIG) [27, 28] (“excellent” (76%–100%), “good” (51%–75%), “fair” (26%–50%), and “poor” (0%–25%)), participants with an average daily device usage of 30 min or more will be classified as having high adherence, while those with less than 30 min per day will be classified as low adherence. These thresholds may be refined based on the statistical distribution of the relevant data at the end of the study.

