### Intervention description {11a}

There are two intervention groups in our study: the DIST Group (use of DIST alone) and the Combined Intervention Group (DIST and Optical Defocusing Technique). Participants in these two groups will be asked to use the device during near work, including online learning, playing online games, reading, and similar tasks, with a minimum daily usage of 1 h.

The DIST group is included to investigate whether projecting near scenes into the distance can effectively delay the onset of myopia. This group is critical for isolating the specific effect of DIST as a standalone intervention, independent of other factors. The use of DIST aligns with emerging evidence suggesting that increasing outdoor-like visual experiences or reducing accommodative stress may mitigate myopia progression.

The Combined Intervention group (DIST and Optical Defocusing Technique) evaluates the synergistic effect of combining DIST with an optical defocusing technique. DIST and the optical defocusing technique can be integrated simultaneously through the optical path system (Fig. 2). The system contains two Liquid Crystal Display (LCD) screens, one of which is used to achieve distant-image display, while the other is used to achieve defocus intervention. LCD-1 functions as the object for the distant-image display, while half-mirror-2, the curved mirror, and the lens together form a convex lens optical system. Based on the principles of geometric optics, LCD-1 is positioned within one focal length of this convex lens system. As a result, the light rays entering the eye are divergent, forming an erect, magnified virtual image that enables the perception of a distant image. Similarly, LCD-2 acts as the object for the defocusing pathway, while half-mirror-1, half-mirror-2, and the curved mirror collectively form a convex lens optical system. By positioning LCD-2 between one and two focal lengths of the convex lens optical system, the light rays entering the eye become convergent, thereby achieving defocusing intervention.

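### The device-usage and near-work subgroup thresholds are called predetermined, yet may be refined from end-of-study data with no requirement that this be done blind to outcomes

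*Protocol article*

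**What the plan says.** All statements are in the protocol article. Unless another section is named, they are in Stratification and definition.

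- Status of the cuts, first statement: "Participants will be stratified into subgroups based on predetermined thresholds for both device usage and near work duration".
- Near-work cut: high intensity means "a daily at-home near work duration of 2 h or more".
- Adherence: "Adherence, defined as the ratio of actual device usage duration to planned usage duration", expressed as a percentage, daily and overall.
- Cited scale: poor 0–25%, fair 26–50%, good 51–75%, excellent 76–100%.
- Cut said to follow from that scale: "participants with an average daily device usage of 30 min or more will be classified as having high adherence". Anyone averaging under half an hour goes into the low group.
- Status of the cuts, second statement: "These thresholds may be refined based on the statistical distribution of the relevant data at the end of the study".
- Required use (Intervention description {11a}): the device is to be used during near work "with a minimum daily usage of 1 h".
- Population: the section puts every participant into this analysis, which on its face includes the control arm.

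The sections Subgroup analysis of secondary outcomes and Statistical procedures apply the groupings to myopia onset, fast progression, change in spherical equivalent and change in axial length.

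**The concern.** A threshold cannot be both fixed in advance and open to change once the data are in. The closing sentence follows both the near-work cut and the adherence cut, so it can be read as covering both. It does not say which data are relevant, who decides, or whether outcomes may be visible at the time. That leaves open choosing the cut that separates the outcomes best and then reporting an ordinary p-value for it.

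Rationale and interpretation says that these results may inform recommendations on near work and on how the device is best used. A chance split by usage could then be read as evidence on how much use is needed.

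The adherence label raises a second, smaller question. It is presented as following a percentage scale but is stated in minutes, and the link between the two is not exact.

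**Working it through.** **1. The two statements on thresholds.** The opening statement fixes the device-usage and near-work cuts beforehand. The closing one lets them be changed at the end of the study. They agree only if the second carries a limit (exposure data only, outcomes unseen, documented before lock). No such limit is written.

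**2. What an open choice of cut could cost.** Inputs:

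- Device users: two arms of 64 (Trial design {8}) with 20% dropout (Adjustment for dropout and attrition): 2 × 64 × 0.80 = 102.4, taken as 102.
- Onset: 21% is the intervention-group rate under Assumed event rate. 35% is my assumption, to give a range.
- Null case: onset unrelated to usage.
- Test: pooled two-proportion z-test, two-sided 0.05, z = (p_a − p_b) / √[p(1 − p)(1/n_a + 1/n_b)], with p the pooled proportion.

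Share of 20,000 simulated null datasets declared significant:

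| How the cut is chosen | Onset 21% | Onset 35% |
|---|---|---|
| Fixed cut at the median | 4.7% | 5.1% |
| Best outcome test of the three quartile cuts | 12.2% | 12.2% |
| Best outcome test of all cuts, 20th–80th percentile | 31.6% | 32.1% |

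A further 10,000 null datasets, with gamma-distributed usage assumed, covered cuts chosen without the outcome:

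| Cut chosen from usage only | Onset 21% | Onset 35% |
|---|---|---|
| Fixed 30 min | 5.1% | 4.9% |
| Sample median | 4.9% | 4.8% |
| Upper tertile | 5.4% | 4.7% |
| Widest gap in usage | 5.1% | 5.0% |

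The second table is what theory predicts: given the usage values, a cut chosen from them alone is fixed with respect to the outcome, so the test keeps its size. The inflation comes from letting the outcome guide the choice, not from the choice being late.

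**3. The 30 min cut against the cited scale.** Adherence = actual / planned × 100. The documents give only a minimum of 1 h; taking planned use as 60 min is an assumption.

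- 30/60 = 50.0%, the top of the *fair* band.
- 29/60 = 48.3%, *fair*; 31/60 = 51.7%, *good*.
- *Good* starts at 0.51 × 60 = 30.6 min and *excellent* at 0.76 × 60 = 45.6 min.

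So at 60 min planned, the group at 30 min or more is *good* plus *excellent*, plus the boundary at 50%. If planned use were longer, the same 30 min would be 30/90 = 33% (*fair*) or 30/120 = 25% (*poor*). A cut in minutes keeps its place on the scale only while planned use is constant.

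**4. Controls.** They have no device and no planned device use, so their ratio is undefined. Classified by minutes, they would all fall below 30 and count as low adherence, which mixes allocated arm with adherence.

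**The case against.** The strongest reply is that, after a section about usage and near-work durations, the relevant data most naturally means the distribution of those durations. Refinement on that basis does no harm, as the second table shows. It is also only a possibility, with fixed cuts as the default, and an analysis plan that is not shown may settle it. This stands as far as it goes: the text does not say that outcomes will guide the cut, and the 31% to 32% is not an expected error rate. What remains is that the sentence does not exclude outcome-guided choice and contradicts the opening statement in the same section. The coded dataset promised under Who will be blinded {17a} hides group identity, not outcomes.

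A reader might infer that any cut set after the data are seen gives invalid p-values. That is too strong, for the reason just given.

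A reader might also infer that the adherence groups are mislabelled as a whole, with *fair* users counted as highly adherent. The document does not support that. At 60 min planned, the split is a natural collapse of four bands into two, and it departs from the scale only at 50%, where a year-long average will seldom fall exactly. The whole-number bands also leave 50% to 51% unassigned. Whether half the required minimum deserves the word *high* is a matter of wording.

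Finally, the dose–response analysis under Statistical methods {20a} suggests quartile groups, a trend test and curve fitting, so it does not depend on the 30 min cut. Regressions on usage and near-work duration are already planned there and in Methods for additional analyses {20b}.

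**Conclusion.** The contradiction is real and lies within one section. It leaves a route to data-driven cuts in subgroup analyses of onset, fast progression, spherical equivalent and axial length. Its size depends on how the route is used: none if the cut comes from exposure data with outcomes unseen, about 12% false positives if the best of three quartile cuts is taken, and about 31% to 32% at worst. These figures are for the binary outcome and assume 102 evaluable device users, onset of 21% to 35% and an unadjusted test.

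The mismatch between minutes and percentages is a boundary point, and it assumes that planned use equals the 1 h minimum. The primary intention-to-treat comparison is untouched. This is a low-severity wording correction.

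**What to change.** 1. Delete the refinement sentence. Alternatively, limit it to refinement from exposure data only, by people who have not seen outcomes, documented before database lock.
2. State the adherence grouping as a percentage of planned use so that it agrees with the cited bands, and reconcile this with the use described under Intervention description {11a}. Which duration counts as planned use is for the investigators to state.
3. Run the adherence analysis within the two device arms.

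The cost is analysis wording only. The downside is that fixed cuts may give subgroups of unequal size; the regressions on usage duration already planned under {20a} and {20b} cover that. There should be time: Trial status dates this version 30 March 2026 and the end of recruitment September 2025, so the last 12-month visits fall around September 2026.
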